#### **8.5.5. Genetics**

ACM patients who have not yet undergone genetic testing will be analyzed by University of Naples Federico II, by whole-exome sequencing. The whole exome will be captured with Agilent SureSelect Human All Exome V6 and each genomic DNA will be univocally tagged with a barcode sequence to allow samples multiplexing during the subsequent sequencing step. The obtained enriched and indexed libraries will be sequenced on an Illumina NovaSeq 6000 System. The results of the analysis of the genes associated to ACM, as for Expert Consensus Statement on the state of genetic testing for cardiac diseases [29], will be recorded in the CRF and used to stratify the patients.

#### **8.5.6. Biomarkers**

Biomarkers will comprise those to determine the safety of the IMP and those which could determine or represent ACM progression, and could eventually influence Atorvastatin effect. They will be searched in plasma or serum.

Beta-HCG, haemochrome, LDL, NTpro BNP, Troponin, CRP, Interleukin6, ST2, CK, AST/ALT, ALP, Bilirubin, LDH, gammaGT, Creatinine, Timp1, PIIINP, will be measured by the diagnostic laboratories of the different centers, using clinical-grade kits. Biomarkers for which standard diagnostic procedures are not on the market or are not usually available in standard clinical labs, will be centrally measured by the research laboratory of Centro Cardiologico Monzino IRCCS, in order to standardize the protocol, with available research-grade Elisa kits. Those includes oxLDL, MDA, 4HNE, Interleukin-6, TNF alfa, TGFβ, BIN1, GAL3, HSP70, estradiol, testosterone. See Annex V for a complete list.

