|                                     |          |    | T2 Visit,
Safety check  | T4 Visit,
Safety check | T9 Visit,
data
collection | T12 Phone
call, safety
check | T15 Phone
call, safety
check | T18 Visit,
data
collection |                                                 |
| Psychological questionnaires        |          | X  |                            |                           | X                               |                                    |                                    | X                                |                                                 |
| Blood withdrawal for genetics       |          | X* |                            |                           |                                 |                                    |                                    |                                  |                                                 |
| Blood withdrawal for ACM biomarkers |          | X  |                            |                           | X                               |                                    |                                    | X                                |                                                 |
| Patient-reported outcome collection |          |    | X                          | X                         | X                               | X                                  | X                                  | X                                | X                                               |
| Study treatment adherence check     |          |    | X                          | X                         | X                               | X                                  | X                                  | X                                |                                                 |
| AE review                           |          |    | X                          | X                         | X                               | X                                  | X                                  | X                                | X                                               |
| SAE review                          |          |    | X                          | X                         | X                               | X                                  | X                                  | X                                | X                                               |

\* only if not preformed previously

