### 7.4. Blinding

The proposed study will be a double-blind study in which investigators and patients are not aware of group assignment. In order to maintain this blind, a 3rd party (Euromed Pharma Services S.r.l.) will be responsible of blinding and distribution to the sites of the study treatment and will endeavor to ensure that there are no differences in time taken to provide to the pharmacies of each site the following randomization:

- Atorvastatin 80 mg and placebo tablets will be indistinguishable in appearance as to maintain the study blind. Also, labelling will not allow to recognize actual treatment.

During the trial, blinding will be broken by the Investigator for emergency purposes only, where knowledge of the blinded treatment could influence further patient care. In addition, CVBF pharmacovigilance will receive safety reports, as per regulatory requirements.

Study blind will be broken after database lock.

In addition, in order to minimize bias in outcome assessment, the following blinding measures will be taken:

- a) Blinded CMR and ECHO core laboratory: CMR and ECHO will be interpreted by 2 expert observers blinded to individual patient treatment assignments in a dedicated core laboratory (at proponent site). The imaging core laboratory is certified by European Society of Cardiology (ESC).
- b) Blinded outcome analysis: an independent professional statistical team will be involved to assess the pre-specified outcomes. The Statistical team will be blinded to individual patient treatment assignments (the analysis will be performed on group A vs. group B, with the exception of Aim3 analysis).

Due to the blinded design of the study breaking code procedures are envisaged. In particular, the blind may be broken if, in the opinion of the investigator, it is in the participant's best interest for the investigator to know the study treatment assignment. The sponsor must be notified before the blind is broken unless identification of the study treatment is required for a medical emergency in which the knowledge of the specific blinded study treatment will affect the immediate management of the participant's condition. The randomization code can be unblinded upon written request to CCM, which retain the assignment correspondence. The date and reason that the blind was broken must be recorded in the source documentation and CRF, as applicable.

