#### **T9 Visit Data collection (9th month +/- 1 month)**

This visit includes:

- IMP supply (3 kits)
- Full physical examination
- Pregnancy test (WOCBP only)
- Blood withdrawal for hepatic and muscle functionality
- 12-lead ECG
- ECHO
- Holter ECG
- ICD/ILR interrogation
- Psychological questionnaires (i.e. SF-36; HADS; IES-R)
- Blood withdrawal for biomarkers
- Patient-reported outcome collection
- Study treatment adherence check
- AE review
- SAE review

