#### **8.5.4. Clinical Safety Laboratory Assessments**

The list of clinical laboratory tests to be performed are provided in the SoA together with the timing and frequency.

The investigator must review the laboratory report, document this review, and record any clinically relevant changes occurring during the study in the AE section of the CRF. The laboratory reports must be filed with the source documents. Clinically significant abnormal laboratory findings are those which are not associated with the underlying disease, unless judged by the investigator to be more severe than expected for the participant's condition.

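### LDL is measured by local laboratories during treatment and nothing withholds the month-9 result from blinded site staff or patients, so they can infer the arm well above chance

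*Protocol*

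**What the plan says.** Section 7.4 defines the blind in terms of the people at the site: "The proposed study will be a double-blind study in which investigators and patients are not aware of group assignment". The measures it gives are identical tablets and labels, a core laboratory that reads ECHO and CMR without knowledge of the arm, and a statistical team blinded to individual assignments. Laboratory results are not mentioned.

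Section 8.5.6 divides the biomarkers by place of measurement. The first list begins with beta-HCG and a blood count and continues "LDL, NTpro BNP, Troponin, CRP, Interleukin6, ST2, CK, AST/ALT, ALP, Bilirubin, LDH, gammaGT, Creatinine, Timp1, PIIINP, will be measured by the diagnostic laboratories" of the centres. A second list, which includes oxLDL but not LDL, "will be centrally measured by the research laboratory of Centro Cardiologico Monzino IRCCS, in order to standardize the protocol".

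The Schedule of Activities has a row "Blood withdrawal for ACM biomarkers" marked at T0, T9 and T18. The visit descriptions in 8.1.4 repeat it; at T9 the item is "Blood withdrawal for biomarkers". T2 and T4 list only the hepatic and muscle tests, plus a pregnancy test where relevant.

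Section 8.5.4, on safety laboratory tests, says: "The investigator must review the laboratory report, document this review, and record any clinically relevant changes". It exempts no analyte and has the reports filed with the source documents.

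Section 3.1 attributes a lipid-lowering effect to atorvastatin. Section 6.2 excludes patients on other lipid-lowering drugs. Section 7.2 foresees no dose modification.

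**The concern.** Identical tablets do not conceal an arm that a routine blood result gives away. Here the drug's best-known effect is on an analyte that the plan sends to the hospital laboratory of the treating site, with a baseline value at T0 and an on-treatment value at T9. Other lipid-lowering drugs are excluded and every active patient is assigned the same fixed dose, so a large fall in LDL has few explanations other than allocation.

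At stake are the outcomes and decisions that rest with people at the site or with the patient over the second half of treatment:

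- causality of adverse events, which the investigator judges (8.3.2.2);
- whether a cardiac event is handled as disease-related or as an SAE, which turns partly on that same causality opinion (8.3.5), and the study stopping conditions, which count drug-related deaths and discontinuations (8.2.1);
- the T18 questionnaires and the patient-reported outcomes;
- discontinuation by the investigator (8.2.3) and background therapy, left to the cardiologist's judgement (7.6).

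Section 5.5 justifies the placebo by the need for a fair estimate of side effects, symptom perception and well-being. Those are the outcomes most open to knowledge of the arm.

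**Working it through.** **Passages set side by side**

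1. Where LDL is measured: the centres' own laboratories (8.5.6). This is a stated choice, made alongside a central route for oxLDL in the same section.
2. When: T0, T9 and T18. T9 is at month 9 with a window of one month either way, so about 18 − 9 = 9 months of treatment remain.
3. Who can see it: 8.5.6 puts LDL in the same local list as CK, AST/ALT and bilirubin and does not separate the reports. Biomarker change is a secondary endpoint (section 4), and 11.1 makes the investigator answerable for CRF accuracy against source documents.
4. What prevents it: nothing in 7.4, 8.5.4 or 8.5.6. Section 8.3.7 restricts access to the treatment codes, which does not cover a laboratory value that points to the code.

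**How informative one LDL result could be**

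The protocol gives no LDL effect, SD or guessing rate, so there is no figure of its own to reproduce. The inputs are:

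- allocation 1:1 (section 7.3);
- between-arm difference in percentage LDL change from T0 to T9, *d*: assumed 30, 40, 50 or 60 points;
- within-arm SD of that change, *s*: assumed 15, 20, 25 or 30 points;
- normal distributions with equal SD, full adherence, and a guesser who cuts midway between the two arm means.

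A patient is then classified correctly when the observed change lies less than *d*/2 from its own arm's mean in the direction of the other arm:

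P(correct) = Φ(*d* / (2*s*))

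For example, *d* = 30 and *s* = 30 gives Φ(0.50) = 0.691; *d* = 60 and *s* = 15 gives Φ(2.00) = 0.977.

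| *d* | *s* = 15 | *s* = 20 | *s* = 25 | *s* = 30 |
|---|---|---|---|---|
| 30 | 0.841 | 0.773 | 0.726 | 0.691 |
| 40 | 0.909 | 0.841 | 0.788 | 0.748 |
| 50 | 0.952 | 0.894 | 0.841 | 0.798 |
| 60 | 0.977 | 0.933 | 0.885 | 0.841 |

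Under a working blind the figure is 0.50.

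**Adherence.** If a fraction *q* of active patients do not take the drug, they look like placebo patients and P(correct) falls by 0.5*q*(2P − 1). Taking *q* = 0.15 purely as an illustration (the size of the protocol's drop-out allowance):

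- lowest cell: 0.691 − 0.075 × 0.382 = 0.66;
- highest cell: 0.977 − 0.075 × 0.954 = 0.91.

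The conclusion does not depend on full adherence.

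**Which result matters.** There is no on-treatment LDL before T9. The T18 sample is taken at the same visit as the T18 ECHO and questionnaires, so its result comes too late to affect them; at most it precedes the month-19 telephone call. The exposure is essentially the T9 value, acting over roughly months 9 to 18.

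**The case against.** A reader might infer more than the text supports, in four ways.

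**That the double blind is defeated outright, primary endpoint included.** The documents do not support this. ECHO and CMR are interpreted by two blinded observers in a core laboratory (7.4). What remains for the primary endpoint is indirect, through drop-out, co-treatment and possibly image acquisition, and no passage says that the person acquiring the ECHO sees the LDL.

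**That investigators are required to review LDL.** The review duty stands under safety laboratory assessments, and the Schedule of Activities keeps the hepatic and muscle draw separate from the biomarker draw. The duty reaches LDL only by inference, because 8.5.6 mixes safety and progression markers. Local measurement makes access likely; it does not make review compulsory.

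**That the statisticians are unblinded.** Section 7.4 says only this: "The Statistical team will be blinded to individual patient treatment assignments". A group-level lipid difference, which appears once blood parameters are analysed, does not break that promise. The order of analyses can be left to the statistical analysis plan.

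**That the guess rates measure bias.** They do not. Every input is assumed, and nothing in the documents allows the effect on adverse event rates, questionnaire scores or drop-out to be estimated.

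Annex V, which 8.5.6 cites for the full list of tests, is available by title only, so the absence of masking is established for the visible text alone.

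These points limit the reach and timing of the problem. They leave standing that the plan, followed as written, produces a strong marker of arm at the site and gives no instruction to withhold it.

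**Conclusion.** The concern holds within limits. Local measurement of LDL at T9, with no masking, conflicts with the protocol's own definition of the blind. Across the assumed range (difference 30-60 points, SD 15-30 points) a single T9 result identifies the arm in about 69-98% of patients, against 50% by chance. Inference for an individual patient remains probabilistic.

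The exposure starts at about month 9 and concerns adverse event causality and disease-related versus serious classification, questionnaires, discontinuation and background therapy. Reading of the primary endpoint is largely protected. Section 9.1.4 already expects more drop-out on atorvastatin and allows imputation for losses after T9, so an indirect route to the primary analysis through attrition exists, but its size cannot be estimated from the documents.

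This is a cheap correction worth making. A T9 result that has been issued cannot be recalled.

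**What to change.** In sections 7.4 and 8.5.6, state that post-baseline LDL is handled in one of two ways:

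- measured centrally, from the T9 and T18 biomarker samples already drawn; or
- measured locally, with the result suppressed on reports to site staff and patients until database lock.

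Keep CK, AST/ALT and the other safety tests local and visible. Add a sentence to 8.5.4 that the review duty does not extend to the withheld lipid results. T9 is the result that matters; applying the rule to T18 as well keeps it simple and covers the month-19 call.

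Costs: no extra blood draw or visit is needed. The central option adds a routine assay to a laboratory that 8.5.6 describes as running research-grade kits; the local option needs a reporting instruction at each centre. Either changes protocol text, so an amendment under 12.3 should be assumed. The downside is that sites do not see lipids during treatment, and the sponsor would have to settle how that is handled.

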#### **8.5.7. Metabolomic Research**

To further dissect the specificity of Atorvastatin on particular lipid pathways, a specific lipidomic signature will be defined in patients at the baseline and in response to the treatment. This will enclose the characterization of several lipid classes, including di- and triglycerides, acylcarnitines, cholesteryl esters ceramides, etc [30]. The definition of a set of dysregulated lipids whose abundance may be rescued after drug administration will provide a collection of analytes with predictive value, providing a description of the metabolic disruptions/restoration. The lipidomic characterization of samples will be performed by University of Naples Federico II, employing the standardized protocols of the MxP® Quant 500 XL kit (Biocrates Life Sciences Innsbruck, Austria), in combination with MS analysis. The kit will allow the analysis of roughly 80 real samples per plate, providing the quantification of more than 1,000 metabolites from various biochemical

classes, with more than 400 quantifiable metabolism indicators covering hundreds of metabolic pathways.

## 9. Statistical Considerations

### 9.1. Sample Size Determination

A power analysis estimated that 88 patients (44 per group) will be sufficient to observe at T18 a significant ( $\alpha=0.05$ ) mean absolute difference between the two groups of 2.4 points of RV free wall longitudinal strain (%), hypothesizing a standard deviation of 4.5% and with a power of 80%. The statistical test used to calculate the sample size was an independent one-sided T test. Assuming a drop-out rate of 15% during the study, the total sample size is 102 patients (51 per group). Assuming a screening failure of about 5%, 110 patients will be screened.

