**Number of Participants:**

Approximately 110 participants will be screened to enroll 102 patients. The final number of needed evaluable participants is 88 (taking into account the drop-outs) for an estimated total of 44 evaluable participants per treatment group.

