## 5.2. Participant and Study Completion

Approximately 110 participants will be screened to achieve 102 randomly assigned to study treatment and 88 evaluable participants for an estimated total of 44 evaluable participants per treatment group.

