### 7.3. Method of Treatment Assignment

All patients who sign informed consent and begin the study screening process will be tracked through a 3-digit identification code that will be assigned at hospital admission at each study site using the electronic Case Report Forms (eCRF). The 1st digit will indicate the study site and the 2nd and 3rd digit numbers the individual patient number. Patients will be randomized 1:1 to determine treatment allocation on top of the conventional therapy. The randomization list will be generated using SAS 9.4 statistical software (version 9.4, SAS Institute, Cary, NC, USA). The randomization scheme will be securely stored at the coordinator centre. Once randomization is completed and a treatment is assigned, crossover will be not permitted. Randomized patients who terminate their study participation for any reason, regardless of whether study intervention was taken/completed or not, will retain their randomization code.

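### Minor correction: 102 randomised, 15% drop-out and 88 evaluable do not agree; at 15% loss, 102 leaves about 86 to 87

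*Protocol*

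**What the plan says.** Section 9.1 fixes the evaluable number: "A power analysis estimated that 88 patients (44 per group) will be sufficient to observe at T18". The inputs are a "mean absolute difference between the two groups of 2.4 points of RV free wall longitudinal strain" and the planner is "hypothesizing a standard deviation of 4.5% and with a power of 80" per cent, with alpha 0.05. The test is named: "The statistical test used to calculate the sample size was an independent one-sided T test". The section then allows for losses: "Assuming a drop-out rate of 15% during the study, the total sample size is 102 patients (51 per group"), and assumes about 5% screening failure to arrive at 110 screened.

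Two other places carry the same counts. The synopsis, under Number of Participants, enrols 102 and says: "The final number of needed evaluable participants is 88 (taking into account the drop-outs"). Section 5.2 says: "Approximately 110 participants will be screened to achieve 102 randomly assigned to study treatment and 88 evaluable participants". Section 7.3 sets equal allocation: "Patients will be randomized 1:1 to determine treatment allocation". No section gives the formula by which 88 became 102.

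**The concern.** Drop-out during the study is a fraction of the patients randomised, so the evaluable number is the randomised number times one minus the drop-out rate. On that definition 102 and 15% do not give 88.

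Two things are at stake. The first is accuracy: the sample-size justification fails a one-line check, and the same mismatch appears wherever the counts are repeated. The second is the power statement, which is tied to 44 evaluable per group. By the t test that the plan names, 44 per group already sits just under 80%, so there is no slack to absorb even a small shortfall.

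**Working it through.** **Inputs.** Section 9.1: difference 2.4 strain points, SD 4.5, one-sided alpha 0.05, power 80%, 88 evaluable (44 per group), drop-out 15%, 102 randomised (51 per group), screening failure about 5%, 110 screened. Section 7.3: 1:1 allocation.

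**Step 1. Reproduce the evaluable number.** By the normal approximation, n per group = 2 x [(1.645 + 0.842) x 4.5 / 2.4]^2 = 43.5, rounded up to 44, or 88 in total. This matches the plan. The noncentral t gives power of 79.9% at 44 + 44 and would need 45 per group to pass 80%.

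**Step 2. Check the drop-out allowance.**

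| Question | Calculation | Result |
|---|---|---|
| Evaluable from 102 at 15% loss | 102 x 0.85 | 86.7 (43.35 per group) |
| Largest drop-out at which 102 still gives 88 | (102 - 88)/102 = 14/102 | 13.7% |
| Randomised number needed for 88 at 15% loss | 88/0.85 = 103.5 | 104 (52 per group) |
| Check of 104 | 104 x 0.85 | 88.4 |

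**Step 3. Where 102 could come from.** Two routes give it:
- 88 x 1.15 = 101.2, rounded up to 102 (per group 44 x 1.15 = 50.6, rounded up to 51);
- 44/0.85 = 51.76, rounded down to 51 per group.

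The protocol does not say which was used. Both fall short of 88 evaluable at 15% loss, so the finding does not depend on the answer.

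**Step 4. Effect on power.** Noncentral t, one-sided alpha 0.05, difference 2.4, SD 4.5:

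| Evaluable patients | Power |
|---|---|
| 44 + 44 | 79.9% |
| 43 + 44 | 79.5% |
| 43 + 43 | 79.0% |

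The loss is about 0.4 to 0.8 percentage points. By the normal approximation it is 80.4% at 44 per group and 79.9% at the expected 43.35 per group, again about half a point.

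**Step 5. Screening.** 110 x 0.95 = 104.5, so the stated screening number already supplies 104. Working back, 104/0.95 = 109.5, which rounds up to 110, while 102/0.95 = 107.4, which rounds up to 108. The figure of 110 therefore fits 104 randomised better than 102.

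**The case against.** The strongest reply is that the gap is trivial and 15% is only a round planning figure. Section 5.5 calls it a conservative allowance. The expected shortfall is 88 - 86.7 = 1.3 patients. If each of 102 patients independently has a 15% chance of loss, the standard deviation of the number lost is the square root of 102 x 0.15 x 0.85, about 3.6. Under that assumption, 102 still has about a 42% chance of yielding 88 or more. This stands as an argument about size. It does not reconcile the figures, because a plan that sets a loss rate should meet its target at that rate. The Missing data section also says that the 15% already covers the extra loss expected under atorvastatin, so it is not spare margin.

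A second reply is that drop-outs may still be analysed: Section 8.2.3 provides for multiple imputation, and the ITT population is everyone randomised who receives study drug. But the Missing data section excludes patients who leave before T9 and makes imputation after T9 optional, and the synopsis presents 88 as the count after drop-outs. Imputation may soften the consequence, but the stated arithmetic still does not close.

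A reader might infer three stronger things that the documents do not support:
- That the trial is materially underpowered because of this. The loss is under one percentage point.
- That the sponsor is known to have multiplied by 1.15. The number is consistent with that, but no formula is given and rounding down explains it equally well.
- That 88 evaluable will certainly be missed. It will be missed on average if losses run at 15%; at 13.7% or less it will be met.

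Whether a one-sided test is appropriate is a separate question and plays no part here.

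**Conclusion.** The point holds as a minor correction. The figures 102, 15% and 88 are mutually inconsistent as written, and nothing in the protocol reconciles them. At the stated 15%, 102 randomised gives about 86 to 87 evaluable patients, one to two short of 88, and one-sided power of 79.0% to 79.5% instead of 79.9%. No analysis, design choice or conclusion of the trial changes.

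This rests on three assumptions: that drop-out is taken from those randomised, that evaluable means not dropped out (as the synopsis uses it), and that the plan's difference, SD and one-sided alpha of 0.05 apply. The arithmetic itself is not in doubt; only the route by which 102 was reached is inferred.

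**What to change.** Align Section 9.1, Section 5.2 and the synopsis in one edit, and state the inflation formula. Any one of these closes the arithmetic:

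- **Keep 102 and restate what it delivers:** about 86 evaluable (43 per group) at 15% drop-out, with about 79% one-sided power. Cost: wording in three places and a marginally lower stated power.
- **Keep 102 and 88 and restate the drop-out allowance as about 13.7%.** Cost: wording, but the 15% also appears in Sections 5.5 and 8.2.3 and under Missing data, and the lower rate would need a reason of its own, since Section 5.5 presents 15% as deliberately conservative.
- **State 104 randomised (52 per group),** which gives 88.4 evaluable at 15% loss. Cost: two more patients and a change to 102 wherever it appears, including Overall Design in the synopsis. The screening target of 110 need not change.
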